#### Secondary outcomes

Testing of the secondary outcome variables is exploratory and the results should mainly be used for exploratory purposes. On this basis, no adjustments for multiple testing will be performed.

The time to complete healing of the reference ulcer between the two randomized groups is an important secondary outcome and will be compared using survival analysis. Kaplan-Meier survival curves will be produced for the 2 groups and the median time to healing with 95% CI presented. Treatment effect will be explored using a Cox proportional hazards model including stratification factors (ulcer size and grade) initially. Participants’ heel ulcers that are not healed will be treated as censored and their date of trial exit, or date of last available assessment, or 168-day/trial cessation, as appropriate, will be used to calculate their duration in the trial. Hazard ratio with 95% CI will be given.

Final ulcer area will be analysed by treatment group for those who remain unhealed at the end of the study, using linear regression. As this exploratory analysis will include a subset of the participants, the analysis will be adjusting for baseline area, and any other variables that are found to be imbalanced at baseline (ANCOVA: on both an ITT and PP basis).

Ulcer related pain (measured on a VAS), will be analysed using linear regression and adjusting for baseline pain score, ulcer area, duration of ulcer, and ulcer type on both an ITT and PP basis.

Scores on standardised scales (EQ-5D) will be calculated in line with the guidelines provided by the original authors. The three domain scores will be calculated on the CWIS for each participant, in line with the standard instructions for use: descriptive statistics will be used to summarise these at each assessment. The standardised areas under the curve (area under the curve for each participant adjusted for the duration of available data) will be reported for both groups and compared using a Wilcoxon rank sum test.

*Secondary variables: Descriptive*

All other variables that will not be modelled formally will be considered descriptively. These are:(i)*Concomitant medications*

All concomitant medications will be listed descriptively by study treatment.(ii)Usual wound assessment and care requirements

Routine data related to the formal assessment of the wound and surrounding skin will be presented descriptively with counts and rates; provision of off-loading will be presented as categorical data with changes to device requirements recorded throughout the intervention period noted.

*Secondary variables: Safety*

ADEs and withdrawals comprise safety data and will be presented in line with standard reporting requirements. SADEs will also be considered and presented by group. Secondary outcome measures (incidence of foot infection, major amputation, minor amputation, revascularisation and falls leading to hospital admission) will be reported.

Using a negative binomial model and adjusting for the same covariates as the primary analyses, the numbers of adverse events in each participant between treatment groups will be compared.

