#### Secondary endpoints

(i)*Ulcer-related outcomes*

Time to healing, change in ulcer area (measured by both acetate tracings and digital images analysed by using appropriate software to define area), infection, major and minor amputation, ulcer recurrence, secondary ulceration on either limb and adverse device effects (ADEs).(ii)*Patient-related outcomes*

Local pain (visual analogue scale; VAS), Euroqol-5D (EQ-5D), Cardiff Wound Impact Schedule (CWIS), hospital admission (relating primarily either to the heel ulcer or not), hospital length of stay and death.(iii)*Cost-effectiveness*

Cost-effectiveness will be assessed by developing a decision-analytic model to estimate costs and health outcomes, including percentage of healed ulcers and Quality Adjusted Life Years (QALYs) gained. Costs will be compared between the two groups using a bottom-up approach from the perspective of UK NHS and personal social services. Data relating to the costs of training professionals and the costs of heel casts and their application will be collected by discussions with relevant clinical and finance staff. Incremental cost-effectiveness and cost-utility ratios will be generated for a series of time horizons (including a lifetime perspective) that reflect management of patients with diabetic ulcers of the heel. The findings will be subjected to a series of one-way sensitivity analyses to determine the degree to which variation in parameter estimates affect the relative cost-effectiveness ratios. The results will be used to model the likely effects over the particular time horizons and costs and effects will be discounted at 3.5%. A probabilistic sensitivity analysis will be conducted to investigate the joint uncertainty in parameter values and cost-effectiveness acceptability curves will be generated. A budget impact analysis will be undertaken for 1-year and 5-year periods and will compare the costs to the health service of the use of heel casts in the management of ulcers of the heel in diabetes.

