#### Randomisation

3.*Visits 2to 13 will be every 2 weeks* (*±4 days*) *to 24 weeks* (*visit 13*)

During each visit a check will be made for healing. If the ulcer is judged healed, it will be confirmed by blinded a clinician within 4 days. It will then be reviewed after two weeks (±4 days) weeks and 4 weeks (±4 days). If the ulcer is thought to remain healed at 4 weeks, healing will be confirmed once more by a blinded clinician. If the ulcer recurs during this period, the participant should return to the intervention phase of the study. If the ulcer does not recur, the participant should continue to collect data for health economic analysis and should be reviewed by the research staff at 12 and 24 weeks, assuming these dates have not already passed.

Other measures to be taken at different visits are charted in Table 1. The wound will be cleaned, debrided (when appropriate), traced and imaged at each visit before being redressed. Patient well-being and function will be documented by completion of EQ-5D and CWIS (weeks 12 (±1) and 24 (±2) only.

For participants randomised to the intervention group, a fibreglass heel cast will be replaced as necessary by trained personnel and the patient/carer will be given written and verbal instructions on its use.

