### Statistical methods

All assumed continuously distributed variables will be investigated with regards to distribution. Transformation to unconstrained scales for ulcer area and VAS for pain will be considered. All continuously distributed variables will be summarised by treatment at measured time points with n = number of subjects, mean, 95% confidence interval (CI) of mean, median, standard deviation (SD), minimum, and maximum. Change from the baseline to the end will also be summarised by treatment with n = number of subjects, mean, median, SD, 95% CI of mean, minimum and maximum. All categorical (discrete including ordinal) variables will be presented in contingency tables showing counts and percentages for each treatment group at all time points.

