## Discussion

Ulcers of the heel constitute a major source of morbidity and cost, and there has hitherto been no specific therapy described. Recently, however, the use of lightweight fibreglass heel casts has been described and has been reported to improve both the incidence and speed of healing. The purpose of this trial is to document the efficacy of this intervention, as well as its cost, when compared to the use of defined criteria of best usual care.

The trial is randomised and while it is not possible to blind either the participant or their carer to the allocated arm of the study, the primary outcome measure (clinical healing) will be confirmed by a blinded observer. All non-clinical measures (including digital images of ulcer, measures of pain and discomfort) will be undertaken by blinded observers.

The study population is designed to be as inclusive as possible, with the aim of maximising the external validity of any findings. Thus, the intention is that as large a percentage as possible of people with diabetes complicated by ulceration of the heel could be included - including those with active infection, as well as those with all but the most severe peripheral arterial disease. This population is, however, one with multiple co-morbidities, a high expected incidence of unrelated illness and hospital admission and a poor overall life-expectancy. It is for this reason that a decision has been made to restrict safety measures to device effects. It is also for this reason that the sample size calculation allows for up to 30% attrition, and this is based on previous experience gained in conducting trials in this area.

While the primary outcome measure is that of healing, the trial includes a number of secondary outcome measures. Principal among these are rate of change in ulcer area - as an indication of the likelihood of eventual healing, and the experience of local pain and discomfort. While most foot ulcers in diabetes are typically painless, those on the heel are often the source of pain or other discomfort and experience reported by those who have used such casts in clinical practice is that reduction in local discomfort is often observed.

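### The only between-arm model of ulcer area is confined to participants unhealed at study end, so it conditions on the primary outcome, is not a randomised comparison, and is not ITT as the protocol defines it

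*Protocol article*

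**What the plan says.** All references are to the protocol article.

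- *Secondary endpoints* lists "change in ulcer area (measured by both acetate tracings and digital images" among the ulcer-related outcomes. It does not state an analysis set.
- *Discussion* gives the outcome weight: "Principal among these are rate of change in ulcer area - as an indication of the likelihood of eventual healing".
- *Secondary outcomes* fixes the model: "Final ulcer area will be analysed by treatment group for those who remain unhealed at the end of the study, using linear regression". It continues: "As this exploratory analysis will include a subset of the participants, the analysis will be adjusting for baseline area". Other variables imbalanced at baseline are added, and the ANCOVA is to be done on both an ITT and a PP basis.
- *Statistical analysis* defines ITT as everyone randomised and has all efficacy variables analysed on that population.
- *Statistical methods* provides descriptive summaries of continuous variables by arm at each time point, and adds: "Change from the baseline to the end will also be summarised by treatment". No between-arm comparison is attached to these.
- *Randomisation* (visits 2 to 13) shows that the data exist: "The wound will be cleaned, debrided (when appropriate), traced and imaged at each visit before being redressed".

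**The concern.** Whether a participant is unhealed at the end is determined after randomisation and is the complement of the primary outcome. If casts affect healing, they also affect who enters the area analysis. The cast-arm ulcers left over may then be a harder-to-heal remnant than the control-arm ulcers left over, and the arm difference mixes the cast effect with that selection. Adjustment for baseline area, which the article offers because the analysis uses a subset, removes only the part of the selection that baseline area explains. It does not touch the tendency to heal that shows itself after baseline.

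Two inconsistencies follow. An analysis that leaves out everyone who healed cannot be ITT under the article's definition. And a single final area in the unhealed delivers neither the listed change in area nor its rate of change over time. At stake is the reading of an outcome that the Discussion calls principal: a real benefit could be understated, missed or, in one extreme case, shown with the wrong sign.

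**Working it through.** **1. The plan's own figure.** Inputs (*Determination of sample size*): 40% v 55% healed, α = 0.05 two-sided, power 80%.

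- Uncorrected n per arm = [1.960·√(2·0.475·0.525) + 0.842·√(0.40·0.60 + 0.55·0.45)]² / 0.15² = 172.8, so 173.
- With continuity correction: (172.8/4)·[1 + √(1 + 4/(172.8·0.15))]² = 185.9, so **186**, as stated.
- 372/0.70 = 531.4 and 372/0.75 = 496, matching the stated 531 and 496.

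**2. Who is analysed.** Unhealed: 186 × 0.60 = 111.6 control and 186 × 0.45 = 83.7 cast, together about **195 of 372** (52.5%). Dropped because they healed: about 74 control and 102 cast.

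**3. Bias without correlation (closed form).** Let latent final log area have SD 1, with healing below a threshold. The thresholds are Φ⁻¹(0.40) = −0.253 and Φ⁻¹(0.55) = 0.126, so the common shift that moves healing from 40% to 55% is 0.126 + 0.253 = **0.379 SD**. The mean among those above threshold c is φ(c)/(1 − Φ(c)): 0.644 at −0.253 and 0.880 at 0.126.

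- Cast shrinks every ulcer by 0.379: the unhealed-only difference is (0.880 − 0.379) − 0.644 = **−0.14**.
- Cast heals a random quarter of the otherwise unhealed (0.60 × 0.75 = 0.45 unhealed): the two unhealed distributions are the same, difference **0**.
- Cast closes only the ulcers nearest healing and changes no other: 0.880 − 0.644 = **+0.24**, so the cast arm looks worse.

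**4. With baseline adjustment (simulation, 186 per arm).** The documents give no baseline-to-final correlation, so 0 to 0.9 is assumed. Entries are the cast minus control difference in SD, with the share of trials nominally significant.

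| Scenario | r = 0 | r = 0.71 | r = 0.9 |
|---|---|---|---|
| Common shift (truth −0.38) | −0.14, 35% | −0.21, 78% | −0.29, nearly 100% |
| Random quarter healed | 0, about 5% | 0, about 5% | 0, about 5% |
| Nearest healing only | +0.24, about 75% | +0.17, 57 to 59% | +0.09, about 38% |

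Repeat runs move the percentages by a few points. A stronger baseline correlation reduces the bias but does not remove it even at 0.9.

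**5. All participants, healed ranked lowest.** The probability that a cast participant has the smaller area, counting ties as half, is 0.5·(0.55·0.40) + 0.55·0.60 + (0.45·0.60)·p, where p is that probability among pairs both unhealed.

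- Random quarter: p = 0.5, giving 0.11 + 0.33 + 0.135 = 0.575.
- Nearest healing: p = 0.75 × 0.5 = 0.375, giving 0.11 + 0.33 + 0.101 = 0.541.
- Common shift: about 0.59 to 0.60 by simulation.

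All exceed 0.50, so the direction of benefit is kept.

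**The case against.** The article calls secondary testing exploratory and says openly that this analysis covers a subset. Healed participants are not ignored: the primary analysis and the time-to-healing analysis compare the randomised groups, and an effective cast would show there. The Discussion values area as a pointer to eventual healing, which chiefly concerns ulcers still open, so an unhealed-only summary is an understandable complement. All of this stands and limits the weight of the point. But exploratory status bears on multiplicity, not on selection bias, and the label ITT remains wrong.

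Four stronger readings are tempting and are not supported.

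- *That the fortnightly areas go unused.* They are summarised by arm at each time point; what is absent is a between-arm comparison.
- *That the endpoint is defined as change in all participants.* The listing does not name an analysis set. Moreover, with baseline area in the model, the arm coefficient is the same for final area as for change on the same scale. The mismatch with change therefore comes from who is included, and the mismatch with rate from using one time point. That the article sets out no rate-of-change model is not in itself an error, since such detail may sit in the analysis plan.
- *That the analysis will hide or reverse a benefit.* Under a common shift the estimate keeps the right sign throughout. It vanishes or reverses only under the other two scenarios, and the reversing one is extreme because the cast then does nothing for any ulcer that it does not close.
- *That an all-participant rank analysis is simply more powerful.* At r = 0.71 it reaches 99% against 78%, but baseline-adjusted healing alone reaches 94% in the same simulation, so much of the gain re-tests the primary outcome.

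**Conclusion.** The point holds as a fault in a stated secondary analysis. The one formal comparison of ulcer area conditions on the complement of the primary outcome, is labelled ITT against the article's own definition, and leaves the listed change and the principal rate of change without a randomised comparison. At the planned rates it uses about 195 of 372 completers. A common benefit of 0.38 SD is estimated as 0.14 to 0.29 SD. A benefit that heals a random quarter of otherwise unhealed ulcers gives about 0. A benefit confined to ulcers nearest healing makes cast ulcers look 0.09 to 0.24 SD larger, nominally significant in about 38% to 75% of trials.

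These sizes rest on a normal latent log area, complete follow-up of 186 per arm and assumed correlations of 0 to 0.9. Which scenario applies cannot be known from the documents. The primary result and time to healing are unaffected, so this is a worthwhile correction and not a threat to the trial's main conclusion.

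**What to change.** Make the between-arm comparison of area an analysis of all randomised participants by assigned arm:

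- Count healed ulcers that remain closed as area 0 (lowest rank).
- Where a healed ulcer has recurred, use the area measured from the week-24 digital image. *Primary outcome* foresees recurrence, and the post-healing part of Table 1 lists an image but no acetate tracing.
- Pre-specify the rank for amputation and for death, with a sensitivity analysis to that choice. It is a choice of estimand, not a neutral correction.
- Use a proportional-odds or rank-based model adjusted for baseline area and grade.
- Handle missing week-24 areas by multiple imputation using the fortnightly areas, given planned attrition of 25% to 30%.
- Present the unhealed-only result as description, without a between-arm test, and do not call it ITT.

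The cost is mainly wording, since the scheduled measurements suffice and no participants are added. Two drawbacks should be stated: the effect is an odds ratio rather than cm², and it partly overlaps the primary outcome.

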### Statistical analysis

Appropriate descriptive statistics will be presented for each variable. Two-sided statistical test will be performed and presented with exact *P*-values, with interval estimates constructed using 95% as the level of confidence.

Descriptive statistics, analytical methods and sample size considerations will be included. The study team together with the investigators will make the decisions regarding individual values belonging to a patient to be excluded from the analysis; for example, out of range values/values that cannot be objectively verified. The investigators will make the final decision regarding coding on the reason(s) for withdrawal. The safety population (SP) will comprise all randomised patients for the study

The intention-to-treat (ITT) population is defined as all subjects who were randomised. Given the study is based on a population with an expected high morbidity, the attrition rate will be monitored closely. If the missing primary outcome data fall within the 20 to 25% level, then ITT will be completed without imputation in the first instance and repeated with multiple imputation as a sensitivity analysis. ITT is equal to SP in this study. Once a participant has a healed wound, which is confirmed as ‘healed’, they will no longer participate in the intervention phase of the study, as they will have achieved the primary outcome. Such participants will be deemed to have completed their participation in the efficacy part of the study and their data will be included in the numbers ‘healed’ by 24 weeks.

Per protocol (PP) population is defined as a subset of ITT population that has completed the treatment period of maximum 24 weeks according to the protocol. The following will be regarded as a protocol violation necessitating exclusion from the PP analysis:

Failure to use the study intervention (fibreglass heel cast) as recommended for more than 7 consecutive days, or for more than a cumulative total of 14 days during the course of the 24-week studyOmission of more than one consecutive scheduled fortnightly assessment by the researcher, or omission of a total of 3 or more of these visits during the 24-week study

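### Quality-of-life AUCs are compared by a Wilcoxon test without baseline adjustment; the test stays valid but loses precision that data already collected would recover

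*Protocol article*

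**What the plan says.** All references are to the Protocol article.

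- **Summary measure** (Secondary outcomes): a standardised AUC, described as "area under the curve for each participant adjusted for the duration of available data".
- **Comparison** (Secondary outcomes): these AUCs "will be reported for both groups and compared using a Wilcoxon rank sum test". No covariate is mentioned. The sentence follows the description of the CWIS domain scores; EQ-5D scoring is described just before, so EQ-5D is probably covered, but this is not explicit.
- **Timing**: both instruments are completed at the week 0 randomisation visit (Study plan; Table 1). After that the Randomisation section specifies "completion of EQ-5D and CWIS (weeks 12 (±1) and 24 (±2) only".
- **Contrast within Secondary outcomes**: ulcer pain "will be analysed using linear regression and adjusting for baseline pain score", and final ulcer area is adjusted for baseline area.
- **Status**: "Testing of the secondary outcome variables is exploratory", without multiplicity adjustment.
- **Reporting standard** (Statistical analysis): tests are accompanied by "interval estimates constructed using 95% as the level of confidence".

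**The concern.** The baseline score is likely to be among the best predictors of a later score on the same instrument. It is collected from everyone, yet a rank sum test cannot use it as a covariate. If the AUC runs from week 0, the baseline score also sits inside the outcome, where treatment cannot change it and where it adds between-patient noise. Pain and ulcer area are handled better in the same section, and no reason is given for treating quality of life differently.

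At stake is the chance of detecting a real difference in named patient-related outcomes. The likely harm is a finding of no clear difference that reflects the choice of analysis rather than the intervention.

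**Working it through.** **The plan's own figure.** The document gives no sample size or power for quality of life. The only available size is the 186 completers per group in Determination of sample size. It reproduces: 40% versus 55%, two-sided 0.05, 80% power gives 173 per group, or 186 with continuity correction. Then 372/0.70 = 531.4 and 372/0.75 = 496, matching the stated 531 and 496. I use 186 per arm only to put power on a realistic scale.

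**Weights.** With scores at weeks 0, 12 and 24, the trapezoid area is 6·Y0 + 12·Y12 + 6·Y24. Divided by 24 weeks, the weights are 1/4, 1/2, 1/4. If only weeks 0 and 12 are available, they are 1/2, 1/2.

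**Assumptions (not in the document).** Equal variances (set to 1), a constant effect d at weeks 12 and 24, complete data, and correlation ρ from 0.3 to 0.7. Correlation is either exchangeable or AR(1), with ρ between adjacent assessments. Information means (effect)²/variance.

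**Formulas, exchangeable case.**
- Unadjusted AUC: effect 0.75d, variance 0.375 + 0.625ρ.
- AUC adjusted for baseline: effect 0.75d, variance 0.375 + 0.625ρ − (0.25 + 0.75ρ)².
- Benchmark, mean of weeks 12 and 24 adjusted for baseline: effect d, variance (1 + ρ)/2 − ρ².
- Rank test relative to a t-test under normality: 3/π = 0.955.

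**Example at ρ = 0.5.** Unadjusted AUC: 0.5625/0.6875 = 0.818. Benchmark: 1/(0.75 − 0.25) = 2. Ratio 0.818/2 = 0.409; times 0.955 = 0.391.

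**Under AR(1).** The AUC variance is 0.375 + 0.5ρ + 0.125ρ² and the benchmark variance is (1 + ρ)/2 − (ρ + ρ²)²/4. At ρ = 0.5: (0.5625/0.65625) × 0.609375 = 0.522; times 0.955 = 0.499.

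| ρ | Information kept, exchangeable | Information kept, AR(1) | Power if benchmark has 80%, exchangeable | Same, AR(1) |
|---|---|---|---|---|
| 0.3 | 0.535 | 0.613 | 53.5% | 59% |
| 0.5 | 0.391 | 0.499 | 42% | 51% |
| 0.7 | 0.238 | 0.339 | 28% | 37% |

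Simulation with 186 per arm and exchangeable correlation gave 55%, 42% and 27% for the planned test, against 79% to 81% for the benchmark.

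**Where the loss arises.** At ρ = 0.5, exchangeable, the factor 0.391 splits into three parts:
- omitting baseline from the AUC analysis: 0.432;
- using an adjusted AUC instead of the adjusted follow-up mean: 0.947;
- using ranks: 0.955.

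The product is 0.391. Keeping the AUC and adding baseline as a covariate is therefore worth a factor of 1/0.432 = 2.32 in sample size. At ρ = 0.3 and 0.7 the factors are 1.67 and 3.83. These factors do not depend on the shape of the effect over time, because numerator and denominator share the same effect.

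**If the AUC excludes week 0.** It is then the mean of weeks 12 and 24. Without adjustment it keeps [(1 + ρ)/2 − ρ²]/[(1 + ρ)/2] of the benchmark information: 0.56/0.65 = 0.86, 0.50/0.75 = 0.67 and 0.36/0.85 = 0.42 at ρ = 0.3, 0.5 and 0.7, before the rank factor. The loss is smaller but does not vanish.

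**The case against.** The other side has good arguments, and several limit the point.

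- **The start of the AUC is inferred.** Neither the starting time nor the trapezoid rule is stated, and an article may leave such construction to a fuller document. This stands as a caveat. The absence of any covariate from the named test does not depend on it.
- **The test is valid.** A reader might infer that chance baseline imbalance biases the comparison. It does not: under randomisation it is random error covered by the type I error rate.
- **Dilution is not a second defect.** Because a constant effect d appears as 0.75d, a reader might infer a separate error of one quarter. A rank test is unaffected by rescaling, a time-averaged score from randomisation is a legitimate quantity, and regression on the AUC would also estimate 0.75d. The weight matters only through the precision already counted above.
- **Ranks are defensible.** They cost about 4.5% under normality and may gain on skewed, bounded scales.
- **Effect estimates are not absent.** A reader might infer that only a P-value will appear. Statistical analysis promises 95% intervals, and Statistical methods promises means with 95% CIs by arm and time point, and for change from baseline. What is not named is an adjusted between-arm difference for this comparison. QALYs belong to a separate decision-analytic model (Secondary endpoints), so nothing there depends on this test.
- **Dropout and death.** A reader might infer that early leavers count as untreated baseline values. Someone seen at weeks 0 and 12 contributes half week-12 data. Someone with baseline only has no AUC, but would have no outcome in a week 12 and 24 model either. Such a model does not score death. Healed participants keep their 12- and 24-week visits.
- **Low stakes.** Secondary tests are exploratory, and Determination of sample size asks for caution with all secondary analyses. This limits severity. It is not a reason to give up precision that costs nothing to keep.

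**Conclusion.** The point holds as one of efficiency, not validity. The plan fixes an unadjusted rank sum test where a baseline score is available and where sister analyses use theirs. For a constant effect, and with the AUC from week 0, the planned test keeps 53.5% down to 24% of the information of a baseline-adjusted analysis (exchangeable), or 61% down to 34% (AR(1)), as the correlation goes from 0.3 to 0.7. The exact loss cannot be fixed from the document, because it states neither the correlation nor the effect pattern nor the AUC construction. It is material throughout that range, and almost all of it comes from omitting baseline. Severity is modest: the comparison is secondary and exploratory, no power is claimed for it, and the primary healing result is untouched.

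**What to change.** Make one of these the main analysis for each CWIS domain and for EQ-5D, chosen before outcomes are examined by arm:

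1. linear regression (ANCOVA) of the standardised AUC on arm and baseline score; or
2. a repeated-measures model of the week 12 and week 24 scores, adjusted for baseline score, ulcer grade and baseline ulcer area.

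Report the adjusted between-arm difference with a 95% CI, by bootstrap if residuals are clearly skewed. The Wilcoxon test can remain as a sensitivity analysis. If the AUC is kept, state its starting time, the integration rule and whether EQ-5D is included. Neither option resolves deaths or participants with baseline only, so their handling needs its own statement.

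The cost is a change of wording and a short analysis program. No extra visits, data or participants are needed, and the primary analysis is unchanged.
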